### Participants

Patients receiving treatment in oncology clinics at Universiti Sains Malaysia and Hospital Seberang Jaya will be recruited for the study. The criteria for study participation include: (1) diagnosed with breast cancer, (2) aged 18 years or older, (3) currently receiving treatment, (4) able to understand and communicate in the study language, and (5) willing to participate in the intervention and follow-up assessments. Patients are deemed ineligible for the study if they: (1) have severe cognitive impairment or significant psychiatric comorbidities (e.g., psychosis, substance abuse) that could hinder their participation in the study, (2) are diagnosed with malignant tumors, and (3) currently receiving any other form of psychological therapy intervention.

Sample size calculations will be based on power analysis using established effect sizes from previous studies on ACT interventions and disease acceptance among similar populations. We conducted an a priori power analysis using GPower 3.1.9.7 to calculate the estimated sample size needed for mixed ANOVA with control of three covariates: the type I error was 0.05, with a power of 0.95, three covariates, with two intervention groups and an effect size of 0.46 by referring to an RCT on the efficacy of ACT on illness cognition among breast cancer patients [28], Hence, the estimated sample size needed is 80 (with the inclusion of a 20% dropout rate). Hence, 40 subjects are required per group.

### Procedure

This research used a consecutive sampling technique for subject recruitment before randomly assigning them to the intervention and control groups. Potential participants will first be screened to determine their eligibility for study participation. Invitations to take part in this trial will follow. The investigator will ensure that participants receive a thorough explanation of the study goals and methods before agreeing to join the study. Participants will sign the Subject Information and Consent Form and Participant’s Material Publication Consent Form before enrolling in the research to indicate their agreement. We will ensure the participants’ anonymity and inform them about their right to withdraw from the study at any point, guaranteeing their confidentiality and autonomy. To ensure participants receive similar intervention, the trial adapts a brief ACT module by Shari et al. [31]. The therapist will administer the intervention when patients are in the hospital for treatment. The assessment batteries will be issued at three specific time points: before the intervention, immediately after the intervention, and three months following the intervention.

Participants in the control group will receive the non-therapeutic approaches, such as reassurance, to allow patients to ventilate their problems and to conduct relaxation techniques such as deep breathing. The intervention and the control groups will receive a 4-session program to ensure ethical considerations and participant access to the intervention. The enrolment, interventions, and assessments of the study are summarized in Fig 1. Fig 2 shows the flow of the research procedures and outcome measures.

**Fig 1 pone.0312669.g001:**
[figure not shown]
Scheduled assessment of the randomized control trial’s outcome measures.

**Fig 2 pone.0312669.g002:**
[figure not shown]
The flow of the research procedures and outcome measures.

## Interventions

### ACT intervention

ACT is one of the most representative experiential behavior therapies in the third wave of cognitive and behavior therapy, called “contextual cognitive-behavioral therapy.” ACT aims to increase psychological flexibility so that people may dedicate themselves to a worthwhile and meaningful life via flexible therapeutic methods, as well as mindfulness, acceptance, defusion, self as context, value, and committed action. The interventions include evaluating cognitive fusion and values, accepting negative emotions and experiences, dissociating from personal experience, contact with the present and meditation training, determining importance, making behavior plans, etc. The ACT intervention is scheduled for 1 session per week for 4 weeks. Each session lasts for 1 hour. The activities in each session are summarized in Table 1. A detailed description of the activities in each session is presented in the S1 Appendix.

**Table 1 pone.0312669.t001:** Summary of content of ACT treatment sessions.

Session	Element in hexaflex	Content
Introductory	Therapeutic relationship, introduction to ACT	Establish a therapeutic relationship, conduct an intake interview (patient’s background, illness, coping mechanisms), develop a case formulation, and introduce ACT principles.
Let it go	Acceptance and defusion	Teach acceptance of unpleasant thoughts and emotions, use metaphors (e.g., tug-of-war with a monster) to practice cognitive defusion, reduce avoidance, and encourage observation of thoughts. Two home exercises on acceptance and defusion provided.
Show up	Contact with present moment, self-as-context	Mindfulness exercises to develop present-moment awareness and non-judgmental observation of thoughts, guide patients to view thoughts flexibly, and practice mindfulness exercises (e.g., mindful breathing).
Get moving	Values and committed action	Help patients identify values, set value-driven goals, guide action steps toward meaningful activities, and provide four home exercises (e.g., values assessment, mindfulness exercise).

### Control group

The control group participants will receive treatment as usual, including nonspecific and nontherapeutic approaches such as providing psychological understanding, identifying current problems, and practising deep breathing exercises. They will receive the same amount of time and attention from the same therapist as the intervention groups and participate in a one-session weekly program for four weeks.

### Treatment fidelity

The ACT intervention group will receive therapy administered by a therapist specifically trained in ACT. This therapist, a PhD student in psychiatry, is not otherwise involved in the study. They have received training from a licensed clinical psychologist with six years of experience in practising ACT. To ensure treatment integrity, independent monitoring will be conducted by a psychiatrist and a clinical psychologist trained in ACT, who will evaluate the delivery of interventions by the therapists in the ACT group. About 15% audio recordings of the psychotherapy sessions will be randomly selected and stratified according to the intervention phase (early, middle, or end). Then, treatment integrity assessments will be performed using (1) the Drexel University CT/ACT Therapist Adherence and (2) the Competence Rating Scale for the selected ACT session recording. Each treatment integrity assessor will assess half of the selected sessions. Then, the inter-rater reliability between the two treatment integrity assessors is computed to assess the treatment integrity of the therapists who are delivering the interventions. If the therapist is inconsistent in delivering some sessions, the therapist will discuss this issue with the principal investigator to solve any shortcomings during the interventions.

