### Blinding

Participants will be unaware of the study’s randomization into the designated groups, which will be carried out by a research assistant who is not otherwise involved. As a result, participants will not be informed of the group to which they are allocated.

Additionally, to minimize bias, the ACT intervention group and the control group will receive a 4-session program (with one hour per session, one session per week for 4 weeks). Participants in the control group will also receive equal attention (attentive listening) and time from the professional figure administering the program with non-therapeutic intervention(the participants in the control group are given equal duration of the session, number of sessions, duration of intervention and attended by the same therapists who conducted the ACT group. The participants will also be attended to with active listening by the therapists in the control group).

To maintain blinding throughout the study, the researchers will be blinded to participants’ randomized assignments into the groups. This process will be carried out by a research assistant who is not involved in the study. Additionally, data collection for this study will be conducted by the same research assistant, ensuring impartiality. The research assistant will remain unknown to the study’s hypotheses. Furthermore, data analysis for the study will be performed by statisticians who are not involved. The statistician will utilize a statistical analysis plan to conduct data analysis before the final unblinding of the data lock.

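### The fidelity plan gives each of two assessors half of the recordings and then computes agreement between them, so as written no session has the two ratings needed, and agreement would not measure therapist integrity anyway

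*Protocol article*

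**What the plan says.** All of the rating plan is in the Treatment fidelity section of the protocol article.

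- **Assessors.** There are two: "independent monitoring will be conducted by a psychiatrist and a clinical psychologist trained in ACT".
- **Selection.** About 15% of the session audio recordings are drawn at random, stratified by early, middle or end phase of the intervention.
- **Scoring.** Adherence and competence ratings are applied to the selected ACT recordings.
- **Allocation of recordings.** "Each treatment integrity assessor will assess half of the selected sessions. Then, the inter-rater reliability between the two treatment integrity assessors is computed". No subset rated by both assessors is described.
- **Planned statistic and its purpose.** "the inter-rater reliability between the two treatment integrity assessors is computed to assess the treatment integrity of the therapists".
- **Follow-up.** If the therapist delivers some sessions inconsistently, this is discussed with the principal investigator.

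On who delivers the sessions, the Blinding section says that control participants are "attended by the same therapists who conducted the ACT group", and the Control group section also has one therapist serving both arms. The Treatment fidelity section, however, describes the therapist who gives ACT as having no other part in the study.

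**The concern.** Two consecutive sentences do not fit together. One divides the recordings between the assessors; the next needs recordings that both have scored. Comparing the two assessors' average scores would not fill the gap, because a difference between averages mixes rater severity with real differences between the two sets of sessions.

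The statistic is also given the wrong job. Adherence and competence scores describe how well the therapy was delivered. Agreement between raters describes only how far those scores can be trusted. A high coefficient is compatible with uniformly poor delivery, and a low one with good delivery that was rated inconsistently.

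At stake is the reliability evidence behind the trial's fidelity claim. It has to be settled while the ratings are being organised, because the planned coefficient cannot be obtained from single ratings afterwards.

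**Working it through.** The plan states no reliability figure and names no agreement coefficient, so there is nothing to reproduce. The check is a count of jointly rated sessions, followed by the precision that double rating would give.

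**Inputs**

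- Participants per arm: 40 (Participants section), or 45 if the 90 in the abstract are split 1:1.
- Sessions per ACT participant: 4 (ACT intervention section).
- Share selected: about 15% (Treatment fidelity).
- Assessors: 2, each rating half of the selection (Treatment fidelity).
- Planned dropout: 20% (Participants section).

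**Step 1: sessions with two ratings, as written**

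Selected = participants per arm × 4 × 0.15. Each assessor rates selected ÷ 2.

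| Participants per arm | ACT sessions | Selected (15%) | Per assessor | Described as double-rated |
|---|---|---|---|---|
| 40 | 160 | 24 | 12 | 0 |
| 45 | 180 | 27 | 13 or 14 | 0 |

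These counts assume that everyone attends all four sessions. If 20% of 40 contributed no sessions, 32 would remain: 32 × 4 = 128 sessions, and 15% of 128 is about 19 recordings. The zero in the last column does not depend on the sample size.

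**Step 2: what double rating would give**

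I use the F-based 95% confidence interval for a one-way ICC with 2 raters and n sessions. The true ICC, ρ, is an assumption; 0.6 and 0.8 show a range.

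- F0 = (1 + ρ) ÷ (1 − ρ), which is 4 for ρ = 0.6 and 9 for ρ = 0.8.
- FL = F0 ÷ F(0.975; n − 1, n) and FU = F0 × F(0.975; n, n − 1).
- Limits = (FL − 1) ÷ (FL + 1) and (FU − 1) ÷ (FU + 1).

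Worked case, n = 24 and ρ = 0.8: FL = 9 ÷ 2.282 = 3.944 and FU = 9 × 2.299 = 20.69. The limits are 2.944 ÷ 4.944 = 0.60 and 19.69 ÷ 21.69 = 0.91.

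| Double-rated sessions | 95% CI if ICC = 0.8 | 95% CI if ICC = 0.6 |
|---|---|---|
| 12 | 0.46 to 0.94 | 0.09 to 0.86 |
| 24 | 0.60 to 0.91 | 0.27 to 0.80 |
| 27 | 0.61 to 0.90 | 0.30 to 0.79 |

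**Step 3: listening time**

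Each session lasts one hour. At 40 per arm, rating all 24 instead of 12 adds 12 hours per assessor. Double-rating only 12 of the 24 means each assessor hears their own 12 plus 6 of the other's, which adds 6 hours.

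**The case against.** **The text does not say that the halves differ.** This is true, and a condensed article may leave a double-rated subset to the full protocol. The supportable statement is that no session is described as double-rated. Even so, a split is the plain reading, since two assessors with half each account for the whole selection. The alternative, that both rate the same half, would leave 12 to 14 deliberately selected recordings unrated, and nothing in the text suggests that. The wrong use of agreement as an integrity measure stands on either reading.

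**Delivery is still monitored.** This also stands. A reader might infer that a null trial result could not be told apart from poor delivery of ACT. The document does not support that: adherence and competence ratings by two assessors are planned, with a corrective step, and they exist whether or not agreement is estimated.

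**The control arm.** A reader might also count it as an error that the evaluation concerns assessors "who will evaluate the delivery of interventions by the therapists in the ACT group" and that the rating covers "the Competence Rating Scale for the selected ACT session recording", so that ACT content reaching control sessions goes unchecked. That is an omission, not a contradiction. It is reasonable to apply an ACT adherence instrument to ACT sessions, and an article may leave control-arm checks to the full protocol. The premise of shared therapists is itself unsettled: the Blinding and Control group sections support it, while the Treatment fidelity section's description of the ACT therapist sits badly with it.

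**Importance.** Randomization, the primary outcome, the sample size and the primary analysis are untouched. I accept that.

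**Conclusion.** The point holds in a limited form. As written, 0 of about 24 to 27 selected recordings are described as having two ratings, so the stated inter-rater reliability cannot be estimated in any of its usual forms. Separately, the section treats rater agreement as the measure of therapist integrity, which it is not.

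The first conclusion rests on reading the two halves as a split of the selection; the second needs no such assumption. The recording counts assume full attendance and would be lower with missed sessions.

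The loss is confined to evidence that the fidelity scores are reliable. The scores remain available. The document does not support the wider inference that poor delivery would go unseen, and unchecked contamination is at most a matter for an optional improvement. The correction is cheap and should be made.

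**What to change.** **Change to make.** In the Treatment fidelity section:

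1. State that both existing assessors independently rate all selected ACT recordings.
2. Name the agreement statistic. An ICC with its 95% confidence interval is suitable, reported as evidence of rating reliability only.
3. Report mean adherence and mean competence scores as the treatment-integrity result.

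**Cost.** About 12 more one-hour recordings per assessor at 40 per arm, or 13 to 14 at 45 per arm, with no new staff. A pre-stated overlap of 12 recordings would add only about 6 hours each, but the interval would be wide: 0.46 to 0.94 even if the true ICC is 0.8.

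**Optional and separate.** Reconcile the statements on who delivers the control sessions across the Blinding, Control group and Treatment fidelity sections. If therapists are shared, rating a sample of control recordings for ACT content would check for contamination. That needs control sessions to be recorded and adds listening time beyond the 12 hours: 15% of the 160 control sessions would be another 24 recordings.

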## Outcomes

Participants will be asked to complete self-report questionnaires in person or through secure online platforms. The questionnaires will cover various aspects, including demographic information such as age, race, educational background, marital status, and employment position. Disease-related information, such as the disease stage, current treatment, and other relevant factors, will also be gathered. Then, we need assessments of the primary and secondary outcomes. We use the electronic data capture system (EDC) to capture and store the data.

### Primary outcome: Disease acceptance

Disease acceptance will be assessed using the Malay version of the Illness Cognition Questionnaire (ICQ-M) for breast cancer patients. Evers created ICQ in 2001, and it assesses disease cognition from both positive and negative viewpoints, with three dimensions of helplessness, acceptance, and perception benefit. The better the condition of the related dimensions, the higher the score [32]. ICQ-M demonstrates strong psychometric properties, making it a reliable and acceptable tool for assessing disease acceptance among breast cancer patients. The ICQ-M exhibited good internal consistency, with Cronbach’s alpha values ranging from 0.742 to 0.927, indicating high reliability across its domains. Content validity was evaluated by a panel of experts who rated the relevance of each item, resulting in high item-level and scale-level content validity indices (I-CVI and S-CVI), affirming the appropriateness of the ICQ-M items. Construct validity was supported by factor analysis, which confirmed the structural integrity of the questionnaire, comprising 17 items distributed across two domains with good convergent and discriminant validity. Additionally, concurrent validity was evidenced by moderate correlations with the Acceptance and Action Questionnaire II (AAQ-II), indicating that the ICQ-M effectively measures the intended constructs in relation to similar tools. The ICQ-M’s reliability and validity make it suitable for measuring disease acceptance in Malay-speaking breast cancer patients [33].

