### Mixed ANOVA analysis

The comparison of mean differences before and post-intervention will be examined to see whether any changes in illness cognition, anxiety, depression, psychological inflexibility, QoL, and social support among breast cancer patients in response to ACT intervention. Then, while controlling for confounders, mixed ANCOVA will be used to look at any significant changes in the measured variables between the waiting and intervention groups, with the group as the between-group factor and time as the within-group factor. A few confounding factors that may affect disease acceptance in cancer will be taken into account and controlled by using mixed ANCOVA, such as the level of pain and fatigue and monthly income [42, 43]. Age is also included as a covariance.

The effect sizes will be determined to evaluate how much patients’ perceptions of the measured variables changed with and without an ACT intervention. The formula of Cohen’s d (Rosnow Rosenthal, 1996) [44] is used to calculate the effect size. According to Cohen (1988), the effect size will be considered small if (d = 0.2), medium (d = 0.5), and large (d = 0.8).

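### The primary outcome is disease acceptance, but the analysis sections test illness cognition, and the ICQ-M score that decides the trial is never identified

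*Protocol article*

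**What the plan says.** - **Construct.** The Abstract, the Primary objective and the heading of the primary-outcome section all name disease acceptance.
- **Instrument.** Under Primary outcome: "Disease acceptance will be assessed using the Malay version of the Illness Cognition Questionnaire (ICQ-M) for breast cancer patients". No subscale, domain, total or item set is singled out.
- **Structure.** The original questionnaire is described this way: "it assesses disease cognition from both positive and negative viewpoints, with three dimensions of helplessness, acceptance, and perception benefit". The Malay version is then described as "comprising 17 items distributed across two domains", and the domains are not named.
- **Direction.** "The better the condition of the related dimensions, the higher the score". Reversal of items is not mentioned.
- **Main analysis.** Mixed ANOVA analysis lists the outcomes as "any changes in illness cognition, anxiety, depression, psychological inflexibility, QoL, and social support".
- **Mediation.** Secondary objectives names disease acceptance as a mediator of QoL. Mediators and moderators tests disease cognition in that role and also makes change in illness cognition a dependent outcome.
- **Sample size.** Participants promises effect sizes for ACT and disease acceptance, then takes 0.46 from a study of illness cognition.

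**The concern.** The article itself treats illness cognition as wider than acceptance. The Introduction describes disease cognition as something that includes acceptance, and the primary-outcome section lists acceptance as one of three dimensions. A test of illness cognition therefore need not answer the primary objective.

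Three things are at stake:

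- **Meaning.** A total score could reach significance through less helplessness or more benefit-finding while acceptance does not move.
- **Power.** If ACT acts mainly on acceptance, a total dilutes the effect for which the trial was sized.
- **Freedom of choice.** Acceptance, either Malay domain and a total all fit the text as candidates. An open choice allows the deciding score to be settled after results are known.

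**Working it through.** **1. Reproduce the planned sample size.** Inputs from Participants: alpha 0.05, power 0.95, two groups, three covariates, effect size 0.46, 20% dropout, total 80. The metric of 0.46 is not named. Read as Cohen's f (so d = 2f = 0.92), in an ANCOVA F test with 1 numerator degree of freedom:

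- noncentrality λ = f²N = 0.46² × 64 = 13.54, with denominator df = 64 − 2 − 3 = 59
- power at N = 64 is 0.951
- with dropout, 64 / (1 − 0.20) = 80, which matches the stated total

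Read as Cohen's d, 0.46 needs 248 (310 with dropout) and does not give 80. I therefore use d = 0.92 and 64 evaluable patients.

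**2. Effect on a total score.** The documents give no ICQ-M subscale SDs or correlations. *Assumptions:* three dimensions, each with SD 1 and equal weight, and a common correlation r of 0 to 0.5 when all are scored in the favourable direction. For a total with helplessness reversed:

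d(total) = (sum of the dimension effects) / √(3 + 6r)

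**3. Only acceptance changes (d = 0.92), helplessness reversed.**

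| Score | r | d | Power at N = 64 |
|---|---|---|---|
| Acceptance alone | any | 0.92 | 0.95 |
| Total | 0 | 0.92/√3.0 = 0.53 | 0.55 |
| Total | 0.3 | 0.92/√4.8 = 0.42 | 0.38 |
| Total | 0.5 | 0.92/√6.0 = 0.38 | 0.32 |

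This loss requires no scoring error.

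**4. Acceptance does not change, helplessness reversed.** The formula is symmetric in the three dimensions.

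- If only helplessness improves by 0.92, the total has the same d of 0.38–0.53, so the chance of a significant result is 0.32–0.55.
- If helplessness and benefit-finding each improve by 0.92, d = 1.84/√(3 + 6r) = 0.75–1.06, and that chance is 0.84–0.99.

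Either result would be reported as a gain in disease acceptance.

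**5. If helplessness were not reversed.** The denominator becomes √(3 − 2r), and the helplessness benefit enters with a minus sign.

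| True benefit (0.92 each) | Reversed total: d; power | Unreversed total: d; power |
|---|---|---|
| All three dimensions | 1.13–1.59; 0.99 or more | 0.53–0.65; 0.55–0.73 |
| Acceptance and helplessness | 0.75–1.06; 0.84–0.99 | 0; 0.05 |
| Acceptance only | 0.38–0.53; 0.32–0.55 | 0.53–0.65; 0.55–0.73 |

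An unreversed total loses more than a reversed one when helplessness also improves. It does not lose more when acceptance alone changes. Direction therefore matters, but which way it matters depends on the pattern of effects.

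**The case against.** The strongest reply is that the article uses the terms loosely and has not chosen a non-acceptance score. The primary objective is acceptance. The Mixed ANOVA section picks covariates because they may affect disease acceptance. The same mediator is called disease acceptance in the objectives and disease cognition in the analysis. Item keys may also sit in a full protocol or SAP that is not shown. All of this is fair: no passage states that a total will be analysed. But the article does state its primary outcome, and it uses terms of different breadth for it. Which score decides the trial should not be left open by that wording.

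A reader might also infer more than the text supports:

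- **That the scoring direction is wrong.** The direction sentence fits a reverse-scored helplessness dimension, where less helplessness gives a higher score. It fails only if raw helplessness is scored upward, and the scoring key is not in the documents. The sentence is unclear, not shown to be false.
- **That the treatment effect will cancel.** This needs both a total score and no reversal, and no passage specifies either. Read literally, a better condition gives a higher score, so all dimensions point the same way.
- **That three dimensions and two domains contradict each other.** The three belong to the original questionnaire and the two to the Malay version. A translation may have a different factor structure. What is missing is the link between them, including whether a separate acceptance domain survives.
- **That several domains will each be tested as primary.** No passage plans this.

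**Conclusion.** The point stands in this form: acceptance is the stated primary outcome, the analysis sections name a broader construct, and the deciding ICQ-M score is not identified. Followed as written, the primary test need not answer the primary objective.

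The size of the problem depends on which score is used. With an acceptance score, planned power is 0.95. With a correctly reversed three-dimension total and an effect on acceptance alone, it is about 0.32–0.55. The same total would also have a 0.32–0.55 chance of significance from helplessness alone. These figures rest on reading 0.46 as f, on 64 evaluable patients, and on the assumed unit SDs, equal weights and correlations. They are illustrations and do not predict this trial's result. If all dimensions improve together, a reversed total would lose no power, but it would still not isolate acceptance.

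The sample-size arithmetic is not in question. What is unconfirmed is whether 0.46 belongs to the score that will be tested.

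**What to change.** 1. Name one ICQ-M score as the primary endpoint: the acceptance items, or the domain of the two-domain Malay version that contains them. First confirm from the validated key that such a score exists.
2. State its items, range and direction, including any reversal, and reword the direction sentence to match.
3. Use that name under Participants (sample size), Mixed ANOVA analysis, and Mediators and moderators, in place of illness cognition and disease cognition.
4. Make the remaining ICQ-M domain or domains secondary.
5. Explain how the three original dimensions map to the two Malay domains.
6. Confirm that 0.46 refers to the chosen score, and name its metric. If it does not refer to that score, restate the power for 80 patients.

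**Cost.** Items 1–5 are wording plus a check of the key, with no new data. Item 6 may show that the stated power of 0.95 does not apply to the chosen score. A subscale has fewer items than the total and may be slightly less reliable.
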